# Umbilical cord mesenchymal stem (stromal) cells to treat lupus nephritis: protocol for a prospective clinical trial

## Study design

This is a proposed protocol for a prospective clinical trial, developed in accordance with the Standard Protocol Items: Recommendations for Interventional Trials (SPIRIT) checklist. The Affiliated Drum Tower Hospital of Nanjing University Medical School (Nanjing, China) acts as the initiating sponsor and coordinator of this trial. The observed group will receive intravenous infusion of Umbilical cord mesenchymal stem cells (UC-MSCs).

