## Subjects Eligibility

Recruitment methodologies include advertisements in academic media as well as liaisons with general practitioners, rheumatologist.

Inclusion criteria are as follows:

(1) Patients with a documented history of fulfilling at least 4 out of the 11 ACR 1997 SLE classification criteria before randomization; (2) Age between 18 and 65 years at the time of obtaining informed consent; (3) Biopsy-confirmed lupus nephritis with pathological classification of Class III, IV, V, III+V or IV+V (2003 ISN/RPS lupus nephritis histological classification criteria), accompanied by active lesions (activity index ≥ 1 and/or increased chronicity index), within 24 weeks; (4) Urine protein/creatinine ratio > 1.0 or 24-hour urine protein quantification > 1.0 g, with or without active urinary sediment containing red blood cell casts; (5) All subjects receiving concurrent treatment with steroids alone or in combination with antimalarial drugs; (6) Meeting one of the following conditions: a. Never received immunosuppressive agents previously. b. Previously received immunosuppressive agents (including CTX, cyclosporine, TAC, MMF, azathioprine, leflunomide, or sirolimus) but had inadequate response or intolerance to treatment; (7) For women of childbearing potential, a negative serum pregnancy test at screening; (8) Willingness to provide written informed consent and comply with the study protocol requirements and restrictions.

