## Exclusion

Exclusion criteria are as follows: (1) Received rituximab or any other B-cell depletion therapy within 24 weeks before screening, or received biologics or small-molecule targeted drugs for immune-related diseases (such as abatacept, infliximab, adalimumab, golimumab, belimumab, tocilizumab, or JAK inhibitors) within 4 weeks before screening, except for herpes zoster vaccine; (2) Received plasma exchange or immunoadsorption therapy within 12 weeks before screening; (3) Prior ineffective or intolerant use of mycophenolate mofetil; (4) Patients with autoimmune diseases other than SLE, including dermatomyositis/polymyositis, mixed connective tissue disease, systemic sclerosis, rheumatoid arthritis, etc., except for patients with secondary Sjögren's syndrome who are allowed to participate in the trial; (5) Blood abnormalities at screening, including any of the following: WBC < 2000/μL, Hb < 6g/dL, PLT < 30000/μL. If any of these abnormalities occur, a repeat screening may be performed, and if the subject meets the inclusion criteria, they can be considered eligible for inclusion; (6) Severe liver or renal impairment at screening, with any of the following abnormalities: total bilirubin > 1.5 times the upper limit of normal (ULN), alkaline phosphatase > 2 ULN, ALT or AST > 2 ULN, eGFR < 30 ml/min or serum creatinine > 265.2 μmol/L. If any of these abnormalities occur, a repeat screening may be performed, and if the subject meets the inclusion criteria, they can be considered eligible for inclusion; (7) Severe uncontrolled cardiovascular disease, neurological disorders, pulmonary diseases (including obstructive lung disease and interstitial lung disease), liver disease, endocrine disorders (including uncontrolled diabetes), or gastrointestinal diseases; (8) Current or recent (within 4 weeks before randomization) severe active or recurrent bacterial, viral, fungal, parasitic, or other infections (including but not limited to tuberculosis and atypical mycobacterial diseases, hepatitis B and C, HIV infection, herpes zoster), or requiring hospitalization and intravenous antibiotic treatment during the screening period; (9) Underwent major surgery within 12 weeks before screening or expected to undergo major surgery during the study period, which is considered to pose unacceptable risks to the patient; (10) Received live vaccines within 12 weeks before randomization or anticipated to receive/require live vaccines during the study period, excluding herpes zoster vaccine; (11) History of malignancies, including solid tumors and hematological malignancies (except for treated and cured); (12) Pregnancy or breastfeeding; (13) If the patients are of reproductive age and do not consent to using effective contraception during the trial.

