
## Intervention

In this study, the intervention factor is UC-MSCs. The UC-MSCs used in the study will be produced by Jiangsu Renocell Biotech Co., Ltd. that conforms to Good Manufacturing Practice standards. UC-MSCs at passages 4 will be utilized, and the transplantation dose will be 2 × 10^6^ /kg cells based on our preclinical study results. To ensure sterility and viability, UC-MSCs will be suspended in 30mL of sterile normal saline and stored at approximately 4 °C during transportation. The stem cell suspensions will be transported as quickly as possible to enable infusion within 12 hours of dissociation. Throughout the six-month intervention period, all subjects will receive the recommended standard of care concurrently with the assigned interventions.

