## Safety indicators and primary and secondary efficacy endpoints

The primary efficacy endpoint of this study is the assessment of the overall response rate (complete response, CR, and partial response, PR) at 24 weeks, defined as a urine protein/creatinine ratio < 0.5, absence of active urinary sediment, and normal serum albumin level. The secondary efficacy endpoints include:

(1) Time to achieve PR and CR in both groups of subjects; (2) Changes in quantified urine protein and/or urine protein/creatinine ratio, serum albumin, serum creatinine, estimated glomerular filtration rate (eGFR), complement levels (C3, C4), autoantibodies (anti-dsDNA, ANA, anti-Smith, anti-RNP, anti-SSA/Ro, anti-SSB/La, anti-phospholipid antibodies) and Coombs test from the screening period to respective follow-up visits; (3) Changes in patient-reported Health Assessment Questionnaire (HAQ) scores and physician's Visual Analog Scale (PhGA-VAS) scores from the screening period to respective follow-up visits.(4) Changes in SLE Disease Activity Index-2000 (SLEDAI-2K), British Isles Lupus Assessment Group-2004 (BILAG-2004) scores, improvement rate in SLE Responder Index from the screening period to respective follow-up visits. (5) Overall response rate (CR + PR) in both groups of subjects at 12 weeks. The safety evaluation includes: (1) Recording of adverse events occurring from the start of subject enrollment until the end of follow-up; (2) Vital sign assessments (blood pressure, pulse, respiratory rate, and temperature) were evaluated every 4 weeks for 24 weeks; (3) Laboratory tests (including complete blood count, urinalysis, liver function, and blood biochemistry) were tested every 4 weeks for 24 weeks.

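### The protocol contradicts itself on whether this is a randomised two-group trial or a single-group before-after study, and it defines neither a comparator nor an allocation method

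*Protocol*

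**What the plan says.** The Study design section calls the study a prospective clinical trial ("This is a proposed protocol for a prospective clinical trial, developed in accordance with the Standard Protocol Items") and describes a single group: "The observed group will receive intravenous infusion of Umbilical cord mesenchymal stem cells (UC-MSCs"). It does not say randomised, controlled or single-arm.

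Other sections presuppose a randomised trial with two groups:

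- Subjects Eligibility, inclusion criterion 1: "fulfilling at least 4 out of the 11 ACR 1997 SLE classification criteria before randomization".
- Exclusion, criterion 8: "Current or recent (within 4 weeks before randomization) severe active or recurrent bacterial, viral, fungal, parasitic, or other infections".
- Exclusion, criterion 10: "Received live vaccines within 12 weeks before randomization".
- Intervention: "all subjects will receive the recommended standard of care concurrently with the assigned interventions". The noun is plural, but UC-MSC is the only intervention described.
- Endpoints section, secondary endpoint 1: "Time to achieve PR and CR in both groups of subjects". Secondary endpoint 5, the 12-week response rate, is likewise reported for two groups.

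The primary endpoint, overall response at 24 weeks, names no group. The Statistical analysis section takes all safety indicators from patients who underwent UC-MSC treatment. It applies a paired t-test to the primary endpoint, the safety indicators and most secondary outcomes.

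**The concern.** The number of groups, and how patients enter them, determines what the 24-week response rate can show. In a randomised trial with a concurrent control, the difference between arms estimates the effect of adding UC-MSC. In a single-group study, the rate describes what happened to patients who received UC-MSC on top of standard of care. Every subject receives standard of care throughout the six-month intervention period, so a before-after change cannot be attributed to UC-MSC rather than to that background treatment.

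The protocol contains parts of both designs and completes neither. A team following Study design and Statistical analysis would run and analyse a one-group study. A team following the eligibility criteria and the secondary endpoints would look for a randomisation step and a second group, and would find neither described.

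**Working it through.** There is no stated figure to reproduce: the protocol gives no sample size, power, response rate or allocation ratio. The check is to set every statement about groups, allocation and comparison side by side.

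| Section | What it states | Reading it fits |
|---|---|---|
| Study design | One group, given UC-MSC; no comparator | Single group |
| Subjects Eligibility, inclusion 1 | SLE criteria met before randomisation | Randomised |
| Exclusion 8 | Infection look-back of 4 weeks before randomisation | Randomised |
| Exclusion 10 | Live-vaccine look-back of 12 weeks before randomisation | Randomised |
| Intervention | Assigned interventions, plural; only UC-MSC described | Hints at two groups |
| Primary endpoint | 24-week response; no group named | Either |
| Secondary endpoints 1 and 5 | Reported for two groups | Two groups |
| Statistical analysis, safety set | UC-MSC recipients only | Single group |
| Statistical analysis, test | Paired t-test, including for the primary endpoint | Single group, before-after |

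Counts over the whole document:

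- Randomisation is mentioned 3 times, each time only as a date in an eligibility criterion.
- Two groups are mentioned 2 times, both in secondary endpoints.
- A comparator is defined 0 times.
- An allocation method is described 0 times.

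Three steps follow.

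1. **The test cannot serve a two-group design.** A paired t-test compares two measurements on the same subject. It does not compare two independent groups of patients. If there are two arms, the named analysis of the primary endpoint does not estimate the difference between them. Its structure suits a before-after analysis, whatever its merits for a yes/no response.

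2. **The safety set cannot serve a two-group design.** If safety indicators come only from UC-MSC recipients, adverse events cannot be set against a concurrent control.

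3. **The dates cannot serve a single-group design.** If nobody is randomised, inclusion 1 and the look-back parts of exclusions 8 and 10 refer to an event that does not occur. The protocol uses screening as a separate anchor in exclusions 1, 2 and 9, so a site cannot assume that screening and randomisation are the same date.

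Neither reading is therefore consistent with all sections.

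**The case against.** The best defence is that randomisation is plainly intended. The word appears three times, interventions are said to be assigned, and the observed group may be loose wording for the treated arm. Study design is silent on allocation and does not deny randomisation. On this view the gap is one of description, to be filled by a statistical analysis plan that is not shown.

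Part of this stands: a randomised trial with undescribed allocation is a plausible reading. But the single-group reading also has direct support in the safety set and the paired t-test, so intent cannot be settled from the text. Nor is this a detail for an analysis plan. Whether a control group exists and how patients are allocated must be fixed in the protocol before enrolment.

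Several stronger readings are tempting and should be resisted:

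- A reader might infer that patients or clinicians choose the treatment, so that the groups are confounded by severity or prior treatment. No section says so, and the only words on allocation point the other way.
- A reader might want to put a size on such confounding. The protocol gives neither response rates by patient type nor a mix between groups, so any figure would rest on invented inputs.
- A reader might say that the endpoints compare the two groups. The two-group wording occurs only in secondary endpoints 1 and 5, and neither states a between-group comparison.
- A reader might say that exclusions 8 and 10 fail altogether without randomisation. Exclusion 8 also covers current infection and events in the screening period, and exclusion 10 also covers live vaccines expected during the study. Only the retrospective parts lose their date.

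**Conclusion.** The contradiction is real and must be resolved before the trial can be interpreted. Study design and Statistical analysis describe a one-group before-after study. Three eligibility criteria and two secondary endpoints describe a randomised or two-group trial, and the Intervention wording leans the same way. With no comparator and no allocation method defined, the protocol as written cannot support a valid between-group conclusion on efficacy or safety.

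The consequence is qualitative: whether a comparative claim is possible at all. The conclusion rests only on the wording of the protocol and needs no numerical assumption. It does not say which design the sponsor intends, and it does not say that allocation is non-random.

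**What to change.** State in Study design which design applies, and bring all the other sections into line. The two routes are alternatives, and the sponsor must say which is true.

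**If the trial is randomised with two groups:**

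- Name both arms and define the comparator, which no section does now.
- State how the sequence is generated, and that allocation stays concealed until eligibility is confirmed.
- Define the primary effect as the between-arm difference in 24-week response, with a 95% CI.
- Replace the paired t-test for the primary endpoint with a two-sample comparison of proportions.
- Collect and report safety data in both arms.

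**If the trial has a single group:**

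- Remove the references to randomisation and to two groups.
- Reconcile the reference date of inclusion 1 and of the look-back parts of exclusions 8 and 10. Which date to use is for the sponsor and investigators to decide.
- Make no comparative efficacy claim.

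**Cost.** If two arms already exist, the cost is protocol wording and a concealed allocation list. If the trial is in fact single-group, the cost is giving up comparative claims; this point does not ask for a control arm to be added.

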## Subjects Eligibility

Recruitment methodologies include advertisements in academic media as well as liaisons with general practitioners, rheumatologist.

Inclusion criteria are as follows:

(1) Patients with a documented history of fulfilling at least 4 out of the 11 ACR 1997 SLE classification criteria before randomization; (2) Age between 18 and 65 years at the time of obtaining informed consent; (3) Biopsy-confirmed lupus nephritis with pathological classification of Class III, IV, V, III+V or IV+V (2003 ISN/RPS lupus nephritis histological classification criteria), accompanied by active lesions (activity index ≥ 1 and/or increased chronicity index), within 24 weeks; (4) Urine protein/creatinine ratio > 1.0 or 24-hour urine protein quantification > 1.0 g, with or without active urinary sediment containing red blood cell casts; (5) All subjects receiving concurrent treatment with steroids alone or in combination with antimalarial drugs; (6) Meeting one of the following conditions: a. Never received immunosuppressive agents previously. b. Previously received immunosuppressive agents (including CTX, cyclosporine, TAC, MMF, azathioprine, leflunomide, or sirolimus) but had inadequate response or intolerance to treatment; (7) For women of childbearing potential, a negative serum pregnancy test at screening; (8) Willingness to provide written informed consent and comply with the study protocol requirements and restrictions.

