## Statistical analysis

Descriptive statistics will be used to summarize baseline characteristics, efficacy outcomes, and safety data. For the safety analysis set, all safety indicators will be obtained from those who have undergone UC-MSC. In the full analysis set, subjects will be excluded if they received no intervention or never gave any evaluation outcome. For the baseline characteristics, continuous variables will be expressed as means ± standard deviations, while categorical data will be given as frequencies. The paired *t*-test will be applied to analyze continuous and categorical variables. For the safety indicators, primary endpoint, and most secondary outcomes, including blood coagulation function, routine tests (blood, urine, and excrement), biochemistry and tumor findings, the paired *t*-test will be used to detect any differences. All statistical analyses will be performed using Statistical Product and Service Solutions (Version 22.0, IBM, New York, NY, USA) by the principal biostatistician. *p* < 0.05 will be considered statistically significant.

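### A patient can enter on 24-hour urine protein alone, with no baseline protein/creatinine ratio, although response is an absolute ratio below 0.5; some may start near that threshold and a few could already meet the whole definition

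*Protocol*

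**What the plan says.** **Entry.** Protocol, Subjects Eligibility, criterion 4: "Urine protein/creatinine ratio > 1.0 or 24-hour urine protein quantification > 1.0 g, with or without active urinary sediment containing red blood cell casts". The two measures are alternatives. Active sediment is optional, no criterion asks for low serum albumin, and no unit is given for the ratio.

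**Primary endpoint.** Protocol, Safety indicators and primary and secondary efficacy endpoints: "assessment of the overall response rate (complete response, CR, and partial response, PR) at 24 weeks". One definition serves both response categories; a responder is "defined as a urine protein/creatinine ratio < 0.5, absence of active urinary sediment, and normal serum albumin level". All three components must hold. There is no 24-hour alternative for the proteinuria component and no required reduction from baseline.

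**Secondary endpoints.** The first is time to partial and complete response in both groups. The second begins "Changes in quantified urine protein and/or urine protein/creatinine ratio, serum albumin", followed from screening to the later visits.

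**Analysis.** Protocol, Statistical analysis, assigns the paired t-test "For the safety indicators, primary endpoint, and most secondary outcomes".

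**The concern.** When response is an absolute threshold, its meaning depends on how far from the threshold each patient starts. Criterion 4 controls that distance only for patients who enter on the ratio: they start at more than twice the responder cut-off. For patients who enter on 24-hour protein, the text requires no ratio above 1.0, none above 0.5, and no ratio measurement at all.

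Three things are at stake:

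- **Response rate.** A patient who starts near the threshold can cross it through ordinary variation in the measurement. One who starts below it, with normal albumin and inactive sediment, is a responder before treatment. Both raise the response rate in either group and shrink a difference between groups.
- **Time to response.** It has no meaning for a patient who meets the definition at entry.
- **Paired comparison.** A paired analysis needs each patient's pre-treatment state on the same definition. Without a screening ratio that state is unknown, and a patient who already meets the definition cannot improve on it.

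A statistical analysis plan cannot repair this afterwards. It can neither supply a baseline ratio that was never measured nor change who was enrolled.

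**Working it through.** The Protocol gives no sample size, power or assumed response rate, so there is no figure of its own to reproduce. The check is whether the entry rule and the endpoint fit together.

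**Inputs from the Protocol:** entry at ratio > 1.0 or 24-hour protein > 1.0 g; response at ratio < 0.5.

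**Assumptions, not in the Protocol:** ratio in g/g; creatinine excretion of 0.8 to 2.2 g/day; log-normal variation of a single ratio with a within-patient CV of 20% to 50%; no true change in proteinuria.

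**Step 1: ratio implied by 24-hour protein.** Ratio = 24-hour protein (g) / 24-hour creatinine (g). At the entry floor of about 1.0 g:

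| Creatinine, g/day | 0.8 | 1.0 | 1.2 | 1.5 | 1.8 | 2.0 | 2.2 |
|---|---|---|---|---|---|---|---|
| Implied ratio | 1.25 | 1.00 | 0.83 | 0.67 | 0.56 | 0.50 | 0.45 |

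A ratio of 1.0 or less needs creatinine of at least 1.0 g/day. A ratio below 0.5 needs creatinine above protein/0.5: more than 2.0 g/day at 1.0 g protein, 2.5 at 1.25 g and 3.0 at 1.5 g.

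**Step 2: chance of a single reading below 0.5 with no true change.** P = Φ(ln(0.5/ratio)/s), with s = √ln(1 + CV²).

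| True ratio | CV 20% | CV 30% | CV 40% | CV 50% |
|---|---|---|---|---|
| 0.67 | 7% | 16% | 22% | 27% |
| 1.00 | <0.1% | 0.9% | 3.6% | 7.1% |

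Example at CV 30%: s = √ln(1.09) = 0.294; ln(0.5/0.67) = −0.293; Φ(−1.00) = 0.16.

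**Step 3: sensitivity to protein at entry.** Same formula, with s set directly to 0.2 and 0.4:

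| Protein, g | Creatinine, g/day | Ratio | P(reading < 0.5) |
|---|---|---|---|
| 1.05 | 1.65 | 0.64 | 11% to 27% |
| 1.05 | 2.07 | 0.51 | 47% to 49% |
| 1.5 | 1.65 | 0.91 | 0.1% to 7% |
| 1.5 | 2.07 | 0.72 | 3% to 18% |

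The problem is concentrated near the entry floor. All of these are chances for the proteinuria component alone. Response also needs normal albumin and inactive sediment, so they are upper bounds on the chance of being called a responder.

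**Step 4: effect on the response rate.** Suppose a share f already meets the whole definition and stays there, and the others respond at rate p. The observed rate is p + f(1 − p), and a difference between groups shrinks by the factor (1 − f). Illustrative rates of 30% and 50%:

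| f | 30% reads as | 50% reads as | Difference, points |
|---|---|---|---|
| 2% | 31.4% | 51.0% | 19.6 |
| 5% | 33.5% | 52.5% | 19.0 |
| 10% | 37.0% | 55.0% | 18.0 |

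The Protocol gives no basis for choosing f.

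**The case against.** The strongest case against is that the effect may be small, and much of it stands:

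- **Three components.** The endpoint is not read on the ratio alone. The other two components protect the endpoint in patients who enter with low albumin or active sediment. Entry does not require either, so the protection is partial.
- **Edge case.** A starting ratio below 0.5 needs more than about 2 g/day creatinine at the lowest qualifying protein, and more at higher protein. Near the threshold is the supportable description; already below it is the exception.
- **Modest dilution.** Even if 5% start as responders, a 20-point difference becomes 19.

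Three stronger readings are tempting, and the Protocol does not support them:

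- **That such patients will be enrolled in number.** The text permits them; it does not show how many there will be.
- **That they bias the comparison if they fall unevenly between groups in a small trial.** The eligibility criteria refer to randomization, and chance imbalance between randomised groups is random error, not bias. No sample size is stated that would make the trial small.
- **That the and/or in the second secondary endpoint pairs one measure at screening with the other at follow-up.** The ordinary reading of "Changes in quantified urine protein and/or urine protein/creatinine ratio, serum albumin" is change in each measure from its own screening value. What does follow is narrower: the wording does not guarantee a screening ratio for every patient.

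**Conclusion.** The point holds as a mismatch between entry and endpoint. The Protocol admits patients on a measure that the response definition does not use, requires no baseline value of the measure that it does use, and sets no required fall. The text therefore allows entry close to the response threshold and, occasionally, with the whole definition already met.

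For a patient at 1.0 g protein and 1.5 g/day creatinine, the chance of an unchanged ratio reading below 0.5 is 7% to 27%, against less than 0.1% to 7.1% at a true ratio of 1.0. These figures assume a ratio in g/g and a CV of 20% to 50%, and they cover the proteinuria component only. The effect on the trial result cannot be derived, because the share entering on 24-hour protein alone is not given. The case for changing the text rests on the endpoint lacking a defined starting point and on the low cost of giving it one, not on a demonstrated large distortion.

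**What to change.** Three changes, made before recruitment:

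1. Measure the protein/creatinine ratio at screening in every patient, by the same method as at week 24, and state its unit. For patients assessed by 24-hour collection, this means adding a creatinine measurement to urine already collected.
2. Add to criterion 4 that the patient must not already meet the primary response definition (all three components) on the last sample before randomisation.
3. In the second secondary endpoint, name the ratio at screening and at each visit as the measure of change in proteinuria. Keep 24-hour protein as descriptive.

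The cost is a urine creatinine on each screening sample, a line or two in criterion 4 and one in the endpoint section, and the loss of a few borderline patients.

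These changes remove patients who are measured as responders at entry and give everyone a baseline ratio. They do not remove patients who start between 0.5 and 1.0, but those patients become visible and can be described. Requiring a ratio above 1.0 from everyone would also remove them. It would change the eligible population, however, so it is more open to debate and is not needed to resolve this point.

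### The stated primary analysis ignores the 6a/6b prior-treatment split known at entry: a small loss of precision, not a bias

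*Protocol*

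**What the plan says.** - **Population.** Protocol, Subjects Eligibility, inclusion criterion 6 requires one of two conditions, 6a or 6b: "Never received immunosuppressive agents previously. b. Previously received immunosuppressive agents". Under 6b the patient has had such agents "but had inadequate response or intolerance to treatment". MMF is among the agents listed in 6b.
- **Restriction on 6b.** Protocol, Exclusion, criterion 3 removes patients with "Prior ineffective or intolerant use of mycophenolate mofetil".
- **Endpoint.** The primary endpoint is the "assessment of the overall response rate (complete response, CR, and partial response, PR) at 24 weeks": one rate over all patients. The secondary endpoints in the same section refer to two groups of subjects.
- **Analysis.** Statistical analysis assigns the paired t-test to a list of outcomes that begins "For the safety indicators, primary endpoint, and most secondary outcomes". It names no stratification factor or covariate.
- **Allocation.** Randomisation appears only as a time reference in the eligibility criteria, for example "at least 4 out of the 11 ACR 1997 SLE classification criteria before randomization". No method, ratio or stratification factor is described, and Study design describes only the group given UC-MSCs.

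**The concern.** Criterion 6 builds two populations into the trial: patients new to immunosuppressants, and patients in whom they have failed or were not tolerated. All subjects also receive standard of care, so it is reasonable, although the protocol does not say so, to expect different background response in the two. If it does differ, prior treatment is a prognostic factor. It is binary and complete for every patient, because it decides eligibility. An analysis that leaves it out carries variance that could be removed at almost no cost.

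The pooled rate also mixes first-line and later-line use, so some description by stratum would help the reader. What is at stake is a modest amount of precision and some clarity of interpretation, not the validity of the comparison.

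**Working it through.** The protocol gives no sample size, power, response rate or stratum share, so there is no figure of its own to reproduce. All inputs below are assumptions.

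**Inputs (assumed).** Two parallel arms, 1:1, simple randomisation; n = 30 to 50 per arm; naive share f = 0.3 to 0.5; response without a treatment effect p1 = 40% in 6a and p2 = 15% in 6b, with 45%/25% and 55%/15% as wider cases. Write p = f·p1 + (1−f)·p2 and d = p1 − p2.

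**1. Share of variance removed by stratifying.** The share is d²·f(1−f) / [p(1−p)], which does not depend on n.
- 40%/15%, f = 0.5: p = 0.275; 0.0625 × 0.25 / 0.1994 = 7.8%.
- 40%/15%, f = 0.4: p = 0.25; 0.0625 × 0.24 / 0.1875 = 8.0%.
- 40%/15%, f = 0.3: p = 0.225; 0.0625 × 0.21 / 0.1744 = 7.5%.
- 45%/25%, f = 0.3: p = 0.31; 0.04 × 0.21 / 0.2139 = 3.9%.
- 55%/15%, f = 0.4: p = 0.31; 0.16 × 0.24 / 0.2139 = 18.0%.
- 10-point gap, mean response 50%, f = 0.5: 0.01 × 0.25 / 0.25 = 1%.

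**2. Power.** For a trial with 80% power unstratified, power after stratifying is Φ(2.80/√(1 − reduction) − 1.96), where 2.80 = 1.96 + 0.84.
- Reduction 7.8%: Φ(2.916 − 1.96) = Φ(0.956) = 83%.
- Reduction 18.0%: Φ(3.092 − 1.96) = Φ(1.132) = 87%.
- Reduction 1%: Φ(2.814 − 1.96) = Φ(0.854) = 80%.

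**3. The chance shift set against total sampling error.** The SD of the between-arm difference in naive share is √(2f(1−f)/n), and the 95% limit of the resulting shift is 1.96 × SD × d.
- n = 30, f = 0.5: SD = 0.129; shift = 1.96 × 0.129 × 0.25 = 6.3 points.
- n = 50, f = 0.3: SD = 0.092; shift = 1.96 × 0.092 × 0.25 = 4.5 points.
- n = 100, f = 0.5, 10-point gap: SD = 0.071; shift = 1.4 points.

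For n = 30 and f = 0.5, the unstratified 95% half-width is 1.96 × √(2 × 0.1994/30) = 22.6 points. With the between-stratum part removed it is 1.96 × √(2 × 0.18375/30) = 21.7 points. The 6.3 points lie inside the 22.6 and combine as squares (22.6² − 6.3² ≈ 21.7²). Stratifying shortens the interval by about 4%.

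**4. Type I error.** Under simple randomisation with no treatment effect, each patient's response in either arm has the same marginal probability p. The unstratified comparison therefore has a null distribution that does not depend on d. A simulation (200,000 runs per setting, f = 0.5, mean response 50%, 20 to 100 per arm) agrees. Unstratified two-proportion z-test: 0.043 to 0.057. Cochran-Mantel-Haenszel test: 0.047 to 0.051. At 50 per arm the unstratified values for gaps of 10, 20 and 30 points were 0.0567, 0.0572 and 0.0574, so the departure from 0.05 comes from discreteness and not from the strata.

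**5. Precision within a stratum.** With 30 per arm and 30% naive there are 9 naive patients per arm. At 40% response the 95% half-width of their difference is 1.96 × √(2 × 0.24/9) = 45 points. With 25 per arm in the stratum it is 1.96 × √(2 × 0.24/25) = 27 points.

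**The case against.** **Chance imbalance looks like a distortion of several points.** A reader might infer that an unequal split of 6a and 6b moves the primary result by several points on top of its stated uncertainty, or biases it. Neither is supported. Under randomisation the imbalance is random error already inside the unstratified standard error, and it does not affect type I error. It is also small with larger arms and smaller gaps. This objection stands in full and limits the point to precision.

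**Every size is assumed.** This also stands. The protocol does not say that response differs between 6a and 6b. Nor is 6b simply a refractory group: it includes intolerant patients, and exclusion criterion 3 narrows it further.

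**Silence on stratification is not a decision against it.** This stands for allocation. A reader might infer that simple randomisation is planned, but the protocol describes no method at all. It stands only partly for analysis. Covariates and subgroups may be left to an SAP that is not shown, but the protocol does name a test for the primary endpoint, and that test has no place for the stratum.

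**The comparison may be within patients.** The paired t-test suggests this, and then between-arm imbalance cannot arise. The references to two groups and to randomisation point the other way. The recommendation is therefore conditional on a two-group randomised design, and settling the design comes first.

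**Stratum results would not show where UC-MSC helps.** This stands at the sizes considered: half-widths of 27 to 45 points cannot locate a benefit. They are useful as description only.

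**Conclusion.** The point holds as a minor one about precision and interpretation. The protocol records a plausible prognostic factor for every patient and then fixes a primary analysis that does not use it.

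With 30 to 50 per arm, 30 to 50% naive and 40% against 15% response, stratifying removes about 7.5 to 8% of the variance, equivalent to roughly 80% rising to 83% power. Over the wider assumed rates the reduction is about 4 to 18%, with power at most 87%. With a 10-point gap it is about 1% and makes no practical difference. These figures assume a two-arm randomised comparison and are not derived from the protocol.

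The documents do not support a finding of bias, of inflated type I error, or of an allocation scheme chosen without stratification.

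**What to change.** 1. Reconcile the listing of MMF in inclusion criterion 6b with exclusion criterion 3, so that membership of 6b is unambiguous before it is used as a stratum.
2. State whether the trial is a two-group randomised comparison. If it is, replace the paired t-test of the primary endpoint in Statistical analysis with wording such as: *Week-24 overall response will be compared between the randomised groups by a Mantel-Haenszel risk difference with 95% CI, stratified by inclusion criterion 6a or 6b. The difference within each stratum will be reported descriptively, without a claim of effect by stratum.*
3. If randomisation has not begun, name 6a/6b as a stratification factor when the allocation method is written. If it has begun, make only the analysis change.

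The cost is one analysis sentence and, where still possible, one factor in the randomisation list. No extra data or patients are needed, because the stratum is already recorded at eligibility.
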